### Demographic and Baseline Characteristics

Demographic variables, such as age, race, and sex, and baseline characteristics, such as medical history, will be summarized by treatment group using descriptive statistics. For quantitative data, this will include the number of observations, the mean, standard deviation, median, maximum and minimum. Qualitative data will be summarised using frequency counts and percentages.

### Safety Analyses

A summary of the number of patients experiencing any adverse event and number of adverse events experienced by patients in each treatment group will be produced. This summary will also show the number of adverse events that were defined as serious and number of patients experiencing SAEs.

The number of patients experiencing each adverse event will be shown using the cross-classification of preferred term (within body system class) by most severe intensity. All adverse events occurring in more than 5% of either treatment group will be summarised, giving the incidence of each event by preferred term.

Serum chemistry and hematology measurements will be listed, with any out-of-range values being flagged as high or low according to their age specific laboratory normal ranges. Values will be summarised by visit using descriptive statistics and shift tables will be produced for each parameter showing the changes with respect to normal laboratory ranges from the baseline visit to Month 12 visit.

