#### Creatine phosphokinase (CPK)

Total CPK, isoenzymes only if total CPK is more than twice the normal upper range.

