### Creatine phosphokinase (CPK):

- CPK elevated factor 3:
  - CPK-control in two weeks
- CPK elevated factor 5:
- Atorvastatin will be reduced from 40mg to 20mg, if the isoenzyme CPK-MB is normal and in the absence of clinical symptoms (e.g. muscle pain, cramps)
- CPK elevated factor 10:
- Atorvastatin will be stopped

After two weeks haematological, serum chemistry and CPK testing will be repeated, and in the absence of normalized values, the Atorvastatin dose will be reduced/stopped until normalization of values is reached.

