# Activities

## Baseline visit (Day 1 visit)

- **The Screening visit is the final visit (month 15) of the SWABIMS-Study !!!**
- Before continuing the medication in the SWABIMS Follow up Study, the patient must give his/her written informed consent to participate.

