## Treatment phase

The treatment phase begins at the Baseline visit (visit month 15 of the SWABIMS-Study) and terminates at months 12 visit.

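### The laboratory shift tables use Month 12 as their only end point and broad normal-range categories, and section 11.1.6 names no analysis of CPK

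*Protocol*

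**What the plan says.** Section 11.1.6 covers laboratory safety in one paragraph. It opens with "Serum chemistry and hematology measurements will be listed, with any out-of-range values being flagged as high or low". A by-visit summary and per-parameter shift tables are then planned, and the latter are described as "showing the changes with respect to normal laboratory ranges from the baseline visit to Month 12 visit". No other laboratory panel is named there.

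Other sections bear on how these tables will read:

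- **Baseline.** Section 10.1 states "The Screening visit is the final visit (month 15) of the SWABIMS-Study", and section 10.2 confirms it: "The treatment phase begins at the Baseline visit (visit month 15 of the SWABIMS-Study) and terminates at months 12 visit". Under section 7.2.2, group 1 has by then taken atorvastatin for 12 months and continues without a break.
- **Entry limits.** Appendix 15.2 accepts ALAT up to 3 times ULN and CPK below 3 times ULN.
- **Visits.** Table 1 schedules the laboratory panels at baseline, Month 6 and Month 12.
- **Dose rules.** Section 8.6.1 ties CPK elevation to repeat testing and, in the absence of normal values, "the Atorvastatin dose will be reduced/stopped until normalization of values is reached". Section 8.6.2 has comparable steps for transaminases and leucocytes.
- **CPK as a panel.** Section 8.2.2 gives CPK its own heading ("Total CPK, isoenzymes only if total CPK is more than twice the normal upper range"). It is not in the serum chemistry list, and Table 1 and the visit lists in section 10 name it apart from serum chemistry.

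**The concern.** Safety and tolerability are stated objectives, and section 8.2.1 makes safety laboratory values one of their three measures. The shift table is the planned display that cross-classifies each patient's status before and after. As specified, it has three weaknesses.

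1. It looks only at the last visit, while the dose rules aim to bring raised values back to normal before then. A Month 6 or unscheduled elevation that was managed successfully is recorded by its two normal ends.
2. Its categories are the normal range only. Within the high category it cannot separate a slight elevation from one that crosses the protocol's own action thresholds.
3. CPK, the muscle marker that drives atorvastatin dose changes, is not among the panels named.

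A reader of the final report could take a quiet shift table as evidence of no laboratory effect when the table could not have shown one. The reader also needs to be told that the reference value in group 1 is an on-treatment value.

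**Working it through.** The protocol gives no figure on this point to reproduce. The check sets the sections side by side and adds two calculations for scale.

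**Coverage of each marker by section 11.1.6, read literally**

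| Item | Liver tests (serum chemistry, 8.2.2) | CPK (own heading, 8.2.2) |
| --- | --- | --- |
| Collected at baseline, Month 6, Month 12 (Table 1) | yes | yes |
| Listing with high/low flags | yes | not named |
| Summary by visit, including Month 6 | yes | not named |
| Shift table, baseline to Month 12 | yes | not named |
| Adverse event if clinically significant (8.5) | yes | yes |

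Serum lipids and TSH are left unnamed in the same way as CPK.

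**What the shift table can record**

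- Normal at baseline, high at Month 6, normal at Month 12: recorded as normal to normal.
- ALAT at 2 times ULN at baseline (allowed by Appendix 15.2) and 6 times ULN at Month 12: recorded as high to high.
- High at both visits at the same level: recorded as high to high, so it stays visible and can be compared with the interferon-only arm.

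**Illustration: temporary excursions seen.** Assume onset uniform over the 12 months and an excursion lasting L months. These are assumptions, since the protocol gives no duration. The share present at Month 12 is L/12. The share present at Month 6 or Month 12 is 2L/12, for L up to 6.

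| L (months) | Month 12 only | Month 6 or Month 12 |
| --- | --- | --- |
| 1 | 8% | 17% |
| 2 | 17% | 33% |
| 3 | 25% | 50% |
| 6 | 50% | 100% |

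Adding Month 6 doubles the share in every row. Unscheduled tests would add more.

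**Is a signal plausible at this size?** Inputs are about 60 patients, half on atorvastatin (section 7), so n = 30, and the rates quoted in section 8.5.6.

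- CK at 3 or more times normal on at least one occasion, about 5%: expected 30 × 0.05 = 1.5; chance of at least one 1 − 0.95^30 = 78.5%.
- Persistent transaminases above 3 times ULN, 0.5%: expected 30 × 0.005 = 0.15; chance of at least one 1 − 0.995^30 = 14.0%.

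Both rates come from general atorvastatin use. Patients who have already tolerated 12 months may have lower ones. On these figures a CPK finding is plausible and has no planned table. For persistent liver elevations, sample size limits detection more than table layout does.

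**The case against.** The strongest reply is that the shift table is one display among several. The same paragraph lists serum chemistry with out-of-range flags, without restricting the listing to scheduled visits, and summarises values by visit, which takes in Month 6. In a trial of about 60 patients a flagged listing can be read in full. Section 8.5 counts a clinically significant laboratory abnormality as an adverse event, section 8.5.1 records study drug action, and section 11.1.6 tabulates adverse events by group, preferred term and intensity. Section 11.1.1 leaves full methodological detail to a statistical analysis plan that is not shown. A baseline-to-end shift is a legitimate description of an extension year, and an on-treatment baseline follows from the design.

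Most of this stands, and it rules out three stronger readings that a reader might infer:

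- **Statin toxicity is hidden by construction.** It is not. Liver tests have the routes just listed, and a clinically significant CPK elevation can reach the adverse event tables.
- **The drug effect cancels because baseline is on treatment.** That would apply to change scores. These tables cross-classify normal-range categories, so a patient high at both visits stays visible.
- **Every elevation that led to a dose change is excluded.** Only those resolved by Month 12 drop out. One still present at that visit appears.

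The reply does not settle the matter, because these routes are partial. A mean over 30 patients dilutes one or two outliers, and a listing is not a comparison between arms. The adverse event route depends on a judgement of clinical significance in a study where the treating physician knows the treatment (section 7.2.4). The listing and by-visit summary, as worded, do not extend to CPK. Nor does the unseen plan dispose of the point, since the protocol itself names the panels and the two visits of the shift table.

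**Conclusion.** The point holds as a moderate, inexpensive improvement to the safety analysis. The Month 12 shift table misses elevations that have resolved and movement within the high category, and CPK has no named laboratory analysis. The first gap is limited for liver tests by the listing, the by-visit summary and the adverse event tables. For CPK only the adverse event route is named.

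The scale is 1.5 expected patients with CK at 3 or more times normal among 30, assuming the 5% rate applies to patients already established on the drug. Under the uniform-onset assumption, half as many temporary excursions are captured as when Month 6 is included. The CPK gap rests on a literal reading of section 11.1.6, and the statistical analysis plan may already close it.

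The shifts describe change during the second year of atorvastatin in group 1. That is not an error, but section 11.1.6 does not state it. A comparison with values before atorvastatin would need parent-study laboratory data from about its month 3, and nothing in the protocol shows that such values exist or can be merged.

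**What to change.** In section 11.1.6, or in the statistical analysis plan:

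1. Name CPK among the parameters that are listed, summarised by visit and tabulated, and say whether serum lipids and TSH are included.
2. Beside the baseline-to-Month-12 shift, tabulate the shift from baseline to the worst post-baseline value over Month 6, Month 12 and unscheduled tests.
3. Count patients per arm who reach the thresholds already in sections 8.6.1 and 8.6.2: CPK factor 3, 5 and 10; transaminases 3 and 5 times the upper limit; leucocytes below 2500 and below 2000. Define for the table what the CPK factor is a multiple of, since section 8.6.1 does not say.
4. State that baseline in group 1 follows 12 months of atorvastatin, so the shifts describe second-year change only. Add a shift from the last pre-atorvastatin parent-study value only if those data exist.

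The cost is table programming, with no new visits, samples or patients; item 4 needs a data merge only if its optional shift is added. There is one downside to manage. The dose rules trigger extra tests, so the atorvastatin arm may be tested more often and would then have more chances of an extreme worst value. Show the worst scheduled value separately from the worst value including unscheduled tests.

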# ETHICS

## Ethical conduct of the study

The planning and conduct of this clinical study are subject to national laws. Only when all of the requirements of the appropriate regulatory authority have been fulfilled will the study begin. The study will be conducted in accordance with the ethical principles of the Declaration of Helsinki and the ICH-GCP Guidelines of 17 Jan. 1997(G.U. n 191, 18 Ago 1997) and with the appropriate national regulations.

## Written Patient information and informed consent form

The investigator will explain the nature of the study, its purpose and associated procedures, the expected duration and the potential benefits and risks of participation to each patient prior to his/her entry into the study (i.e. before examinations and procedures associated with selection for the study are performed). The investigator will provide the patient with an IRB/IEC-approved patient information and informed consent form. Each patient will have ample opportunity to ask questions and will be informed about the right to withdraw from the study at any time without any disadvantage and without having to provide reasons for this decision.

Following this informative discussion a patient will be asked if he/she is willing to personally sign and date a statement of informed consent. Only if the patient voluntarily agrees to sign the informed consent statement, and has done so, may he/she enter the study. The patient will receive a copy of his/her signed and dated form.

## Confidentiality

The protocol data provided for this study to Ethics committee and investigators staff are confidential. Investigators must assure anonymity to the patients. For this reason the documents sent to the sponsor will be identify only with initial letters of patient. However the investigator must archive the listing of the identities of patients involved in the study.

# List of Abbreviations

| ACTH | Adrenocorticotropic hormone |
| --- | --- |
| AE | adverse event |
| ALAT | alanine aminotransferase |
| ANC  Anti-MBP  anti-MOG  ASAT  BOD | absolute neutrophil count  antibodies against myelin basic protein  antibodies against myelin oligodendrocyte glycoprotein  aspartate aminotransferase  burden of disease |
| BRM | biologic response markers |
| CHO | Chinese hamster ovary |
| DC  CIITA  CNS  CPK | dendritic cells  class II transactivator  central nervous system  creatine phosphokinase |
| CRA  CRF  CRO | Clinical Research Associate  Case Report Form  Contract Research Oranization |
| EAE | Experimental Allergic Encephalomyelitis |
| EDSS | Expanded Disability Status Scale |
| ECG  eNOS  iNOS  eod | Electrocardiogram  Endothelial nitric oxide synthase  Inducible nitric oxide synthase  every other day |
| EOS  EP  FAS | end of study  Examining physician  Full Analysis Set |
| FDA  FOV | Food and Drug Administration  Field of view |
| GCP  Gd  GGT | Good Clinical Practice  Gadolinium  gamma-glutamyltranspeptidase |
| Hb  HCG  HDL  HMG-CoA | Hemoglobin  human chorionic gonadotropin  High-density lipoprotein  3-hydroxy-3-methylglutaryl-coenzyme A |
| ICH  IDL | International Committee on Harmonization  Intermediate-density lipoprotein |
| IEC  IFN  IL | Independent Ethics Committee  Interferon  Interleukin |
| IM | Intramuscular |
| IMB | Independent Monitoring Board |
| IRB  ITT | Institutional Review Board  Intent to treat |
| IU  iv | International units  intravenous |
| LDL  LFA-1 | Low- density lipoprotein  Leukocyte Function Antigen-1 |
| MHC | major histocompatibility complex |
| MIU  MMP-9 | million international units  matrix metalloproteinase 9 |
| MRI  MRI-AC | magnetic resonance imaging  magnetic resonance imaging – Analysis Center |
| MS | multiple sclerosis |
| MSFC | multiple sclerosis functional composite score |
| Nabs | neutralizing antibodies |
| NSAID  PBMC  PP-MS | Nonsteroidal anti-inflammatory drug  Peripheral Blood Mononuclear Cells  Primary progressive multiple sclerosis |
| QOL  RBC  RR-MS | Quality of Life  Red blood cells  Relapsing-remitting multiple sclerosis |
| SAE | serious adverse event |
| sc  SP-MS  STAT  TG  TGF | subcutaneous  Secondary progressive multiple sclerosis  Signal Transducer and Activator of Transcription  Triglycerides  Transforms growth factor |
| TNF  Th1  Th2  TP  TSH  VLDL | tumor necrosis factor  CD4+ helper T cells type 1  CD4+ helper T cells type 2  Treating physician  Thyroid-stimulating hormone  Very-low-density lipoprotein |
| WBC | white blood cells |

# Appendix

## Magnetic Resonance Imaging

### Overview

In this multicenter trial, scans will be assessed centrally for number and volume of lesions and for normalized brain volume. For central assessment it is of vital importance that all scans adhere to the standardized MRI protocol, which might be different from the standards otherwise used.

T1-weighted (after Gadolinium injection) and dual-echo MRI scans of the brain will be

performed at screening in order to check MRI inclusion criteria (the inclusion criteria will be assessed locally at the MRI site); this scan will also serve as the baseline scan.

Each center should use the same scanner for each patient for the entire duration of the study. All scanners should have at least 1.0 Tesla magnetic field strength. The following institutions will be involved in the central assessment of the MRI images:

The MRI Analysis Center (MRI- AC) at Bern will perform the entire MR image analysis.

Quality control of the images and data conversion if necessary will be performed by

the sponsor, or by the MRI Core Lab.

### Scanning requirements

###### Procedure

Given the importance of careful repositioning for serial MRI lesion counting and load assessments, great care should be taken when positioning the patients in the scanner and head holder. The following rules apply to all centers:

- Check that the patient can successfully undergo MRI examination
- Enter the patient data into the scanner console, using:
- Patient initials (first letter of given name, first letter of surname)
- Study number, center number, patient number
- Date of birth (dd / mm / yyyy)
- Sex (m/f)
- Scan number (use progressive numbers starting from –1 for the screening scan. If a scan is rejected and has to be repeated the letter R will be added to the scan number, *e.g*.
- 1R1 for the first repetition of the screening scan, -1R2 for the second repetition of the screening scan)
- Explain the scanning procedure to the patient and position her/him in the scanner in the most comfortable position.
- Insert an intravenous needle in the patient’s arm and connect it with a long-line catheter to a drip-infusion of saline; for contrast injection the operator will be able to use the long-line without moving the patient table from the scanner.
- Position the patient’s head and align it in the machine using land-marking devices provided with most of the equipment.
- Position the patient’s eyebrows at the center of the coil and make sure that the horizontal light beam runs over the eyebrows and as close as possible to the line marking the coil center.
- Position the nose along the Z axis of the scanner, *i.e*. make sure that the vertical light beam runs over the nose.
- Use foam cushions and strips to hold the patient’s head in the set position.
- Move the patient into the scanner.

### Imaging

The following order for sequences has to be kept:

1. T1-weighted axial scout

2. T1-weighted coronal scout

3. T1-weighted sagittal scout

4. Rapid T1-weighted SE or T2-weighted FSE/TSE axial (for repositioning check)

5. T2-weighted FSE/TSE

6. T1-weighted SE post gadolinium

Sequences 1 to 4 are performed to obtain reference images for patient repositioning.

### Sequence parameters, T1 axial scout:

- – TR: 100
- – TE: 10-20
- – Slice number: 3
- – Slice thickness: 5mm
- – Orientation: axial
- – Field of view (FOV): 210-230 mm
- – Matrix: 128 x 256
- – Inter-slice gap: 5 mm
- – Number of acquisitions: 1
- – Phase encoding: L > R

### Sequence parameters, T1 coronal scout:

Using sequence 1 as a reference, make a coronal scout, parallel to the brain transverse diameter and depicting the midline of the brain best (*i.e*. at the level of the brainstem); the acquisition parameters will be the following:

- – TR: 100
- – TE: 10-20
- – Slice number: 1
- – Slice thickness: 5 mm
- – Orientation: coronal
- – Field of view (FOV): 210-230 mm
- – Matrix: 128 x 256
- – Number of acquisitions: 1
- – Phase encoding: L > R

### Sequence parameters, T1 sagittal scout:

From the coronal scout make a sagittal scout image, aligned with the falx cerebri and other midline structures, following these parameters:

- – TR: 500-650
- – TE: 10-20
- – Slice number: 1
- – Slice thickness: 5 mm
- – Orientation: sagittal
- – Field of view (FOV): 210-230 mm
- – Matrix: 128 x 256
- – Number of acquisitions: 1-3
- – Phase encoding: A > P

### T1-weighted images to check correct positioning:

On the sagittal scout image previously obtained, position the axial image group, placing the center of the slice group at the inferior borders of the corpus callosum genu and splenium. The slice group will be positioned to include the whole brain from the vertex to the level of the foramen magnum. Save the localizer image with the slices shown on it, to achieve the same slice positioning on subsequent scans; then make a rapid series of either T1-weighted or T2-weighted images (according to site preference) in order to check the correct positioning of the slices. The following parameters should be used:

- – TR: 500-600
- – TE: 10-20
- – Slice number: 22
- – Slice thickness: 3 mm
- – Orientation: axial
- – Field of view (FOV): 250 mm
- – Matrix: 140 x 256
- – Inter-slice gap: 3 mm
- – Series: interleaved
- – Number of acquisitions: 1
- – Phase encoding: L > R

### T2-weighted images to check the correct positioning:

For T2-weighted images, a fast spin echo (or turbo spin echo) sequence should be used with the following parameters:

- TR: 1800-2800
- TE: either single-echo or dual-echo (according to site preference):TE first echo: 30-50; TE second echo: 60-100
- ETL: according to site preference
- Slice number: 22
- Slice thickness: 3 mm
- Orientation: axial
- FOV: 250 mm
- Matrix: approximately 140 x 256.The number of phase-encode lines will depend on the exact sequence used
- Inter-slice gap: 3 mm
- Series: interleaved
- Number of acquisitions: 1
- Phase-encoding: L > R

**Note:** This first series of T1- or T2 axial images is only performed at the baseline scan and then used as a positioning reference for subsequent serial scans.

### Dual-echo images:

Record the slice positioning parameters (shift and rotation angle) of this series and use them for the subsequent series of the same scan (not necessary if the scanner has a repeat or history function). If possible, to speed up the examination, use a rectangular 3/4 FOV (*i.e*., reduce the phaseencoding matrix by 25%) for all subsequent series of axial images. With 3/4 FOV, the FOV is 187.5 in L > R direction and 250 mm in A > P direction; matrix is 256 (read) x 192 (phase). The scanning procedure is resumed with two interleaved series of fast or turbo spin-echo dual echo sequences. Conventional spin-echo sequences are acceptable if fast imaging is not available. The image parameters are as follows:

- TR: 2200-3000
- TE: 15-50/80-120
- ETL: 4-6
- Slice number: 22
- Slice thickness: 3 mm
- Orientation: axial
- FOV: 250 mm
- Matrix: 256 x 256 (192 x 256 if RECFOV)
- Inter-slice gap: 3 mm
- Series: interleaved
- Number of acquisitions: 1
- Phase encoding: L > R
- Presaturation slab/flow compensation: Yes

The axial presaturation slab (50 to 80 mm) must be positioned inferior to the slice group to suppress flow-related artifacts. The second series is performed with the slice position shifted 3 mm caudally compared with the first one, so that when both series are combined, the whole brain is covered. Some General Electric and Philips scanners allow the two separate acquisitions (each of 22 slices) to be performed sequentially and automatically from a single prescription. If the scanner used allows the acquisitions to be split automatically in this way, then this should be done.

Perform a bolus injection of high concentrated gadolinium (i.e. 1.0 mol/L, gadobutrol (gadolinium-DO3A-butriol) using the intravenous long-line and without moving the patient from the scanner. Use contrast at a dose of 0.2 mmol of gadolinium per kilogram of body weight (*i.e*. 0.2 ml/kg). After a post-injection delay of 5 minutes, complete the scanning with postgadolinium T1-weighted SE images. The following parameters should be used.

